### Randomisation, blinding and sample size calculations

Households will be the unit of randomisation of this study. Participating households will be blinded to the type of ITN they received while data collectors will be blinded to the allocation of households to the study arms. Study nets (DuraNet® Plus and DuraNet®) will be identical in appearance. Two cohorts of nets of each ITN type will be followed; cohort 1 to assess ITN survivorship, attrition and Fabric integrity and cohort 2 for nets to be withdrawn for assessment of bioefficacy and insecticide content. A sample size of 510 households per study arm was found sufficient to detect a 7 points difference in ITN functional survival rate over 3 years between households receiving DuraNet® Plus and those receiving DuraNet® with 80% power, assuming a baseline 3-year survival rate of 25%. This sample size was increased by 100 households to account for loss to follow up over time. To account for nets to be withdrawn for bioefficacy studies, hut trials and insecticidal content, an additional 310 households per arm will be included in the study, hence a total of 920 households will be recruited per study arm at each site. It is estimated that about 3 nets will be required per household therefore the study will require 2,760 nets of each ITN type at each study site.

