#### Follow-up for ITN attrition

Net attrition rate in households will be measured by recording the physical presence of the net at 6-, 12-, 24- and 36-months post ITN distribution. All households in cohort 1 will be visited and nets assessed for attrition at each timepoint by recording the physical presence/absence of each net attributed to the household. Where a net is not found, the householder will be questioned about the reason for the loss of the net e.g. given away, sold, stolen, worn out and disposed of etc. Any study nets which have never been used, will be recorded and excluded from the analysis. ITNs lost due to wear and tear will be considered as lost due to attrition, and those lost because they were stolen, sold or given away to others, will be considered as lost to follow-up. During these surveys, a questionnaire adapted from WHO guidelines will be used to collect data on the number of washes and washing practices for the nets found in each household. The household surveys will be conducted by an experienced socio-anthropologists.

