### Data management and analysis

Household data collected during the census and ITN follow up surveys will be captured on electronic forms using smartphones installed with OpenDataKit (ODK) Collect in Benin and by paper forms in Cameroon and Tanzania. Data from the surveys at 12, 24, and 36 months will be used to calculate attrition, functional survival and median survival time using Kaplan–Meier estimators. For functional survival, nets reported as given away, sold, or stolen will be excluded from the analysis. Negative binomial regression will be used to compare hole surface area between DuraNet® Plus and DuraNet®. Data on WHO bioassays and tunnel tests will be obtained from 30 nets of each product type sampled at each time point. A chi-squared test will be used to assess the proportion of nets of each ITN type passing the WHO criteria for alphacypermethrin and PBO bioefficacy based on combined cone and tunnel tests. Proportional outcomes (mortality, blood-feeding, exophily) from the experimental hut trials will be compared at each time point using mixed effects logistic regression, with huts, sleepers, net replicate and nightly observational error included as random-effects while numerical outcomes (entry) will be compared with negative binomial regression. A separate model will be fitted for each outcome to determine whether there is a significant change in improved mosquito mortality achieved DuraNet® Plus compared to DuraNet® over time and between the three countries. All analysis will be performed on STATA version 17.

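### The hole-area comparison between arms has no household term, although households are randomised and each receives about 3 nets of one type

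*Protocol article*

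**What the plan says.** Under Randomisation, blinding and sample size calculations, the protocol article states: "Households will be the unit of randomisation of this study". It adds: "It is estimated that about 3 nets will be required per household". Under ITN distribution and net master lists, allocation is by household, so all study nets in a home belong to one arm, and each net's identifier contains the household number.

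Outcomes are recorded net by net. Attrition is measured by "recording the physical presence/absence of each net attributed to the household", and the fabric-integrity section has every cohort 1 net inspected at 6, 12, 24 and 36 months.

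Under Data management and analysis, the only between-arm model named for these nets is: "Negative binomial regression will be used to compare hole surface area between DuraNet® Plus and DuraNet". For attrition, functional survival and median survival time, the section names Kaplan-Meier estimators and no between-arm test. The same paragraph gives the hut-trial proportions a mixed-effects logistic model with hut, sleeper, net replicate and nightly error as random effects.

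The sample size is counted in households: "A sample size of 510 households per study arm was found sufficient to detect a 7 points difference in ITN functional survival rate". The power is set at 80% and the assumed 3-year survival in the reference arm at 25%. No ICC or design effect is given.

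**The concern.** The unit randomised is the household and the unit analysed is the net. Nets in one home share washing, care and housing, which the Discussion itself names as influences on durability. Their hole areas are therefore likely to be positively correlated. A negative binomial model fitted to nets with its default variance counts three correlated nets as three independent pieces of evidence. Its standard errors are then too small and its p-values too low.

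Physical durability against the reference net is part of the overall aim, and the Background says that such comparisons are needed for procurement decisions. The risk is that a difference in fabric integrity between the two products is declared when it reflects only variation between households.

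**Working it through.** **Inputs from the protocol article.** Randomisation by household; about 3 nets per household; 510 households per arm, to which "This sample size was increased by 100 households to account for loss to follow up over time", giving 510 + 100 = 610 cohort 1 households; a further 310 for withdrawn nets, so that "a total of 920 households will be recruited per study arm at each site" (610 + 310 = 920). Cohort 1 nets per arm and site: 610 × 3 = 1,830.

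**Assumed.** The ICC (a range is shown), and a two-sided 5% test, because the article states neither alpha nor sidedness.

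**1. The plan's own figure.** The standard two-proportion formula for 25% against 32%, 80% power and one observation per household gives 514 per arm with a one-sided 5% test, within 3% of the stated 510. Two-sided it gives 652 (540 for 25% against 18%). The stated number therefore matches a count of one observation per household with a design effect of 1. It takes no credit for multiple nets, and it offers no ICC to use in the analysis.

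**2. Effect of ignoring household.** With m observed nets per household, the design effect is DE = 1 + (m − 1) × ICC. The naive standard error is 1/√DE of the correct one, and the true two-sided error of a nominal 5% test is 2 × (1 − Φ(1.96/√DE)). For m = 3, DE = 1 + 2 × ICC:

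| Assumed ICC | DE | Naive SE / correct SE | 1.96/√DE | True type I error |
|---|---|---|---|---|
| 0.05 | 1.1 | 0.95 | 1.87 | 6.2% |
| 0.1 | 1.2 | 0.91 | 1.79 | 7.4% |
| 0.2 | 1.4 | 0.85 | 1.66 | 9.8% |
| 0.3 | 1.6 | 0.79 | 1.55 | 12.1% |

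**3. Check on the named model.** Hole-area counts were simulated with no product difference: 200 households per arm, 3 nets each, 600 runs per setting. Monte Carlo error is about 1 percentage point.

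| ICC | Negative binomial, nets as independent | Same model, household-clustered SE |
|---|---|---|
| 0 | 5.3% | 5.8% |
| 0.10 | 6.2% | 4.5% |
| 0.19 | 11.2% | 6.5% |
| 0.31 | 11.8% | 5.2% |

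The simulated inflation follows the formula within simulation error, and clustering on household brings the error back to about 5%.

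**4. Late surveys.** Holes can be scored only on nets still present, so m falls over time. As an extreme illustration, suppose only 250 of an arm's 1,830 nets remained (250 is the minimum in the fabric-integrity section) and losses were independent within homes. The retained fraction is 250/1,830 = 0.137, and the size-weighted number of nets per household is 1 + 2 × 0.137 = 1.27. At ICC 0.3, DE = 1 + 0.27 × 0.3 = 1.08 and the type I error is about 6.0%, not 12.1%. If nets in one home tend to be lost or kept together, the value lies between the two.

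**5. Power is a separate matter.** Allowing for household, 510 households with 3 nets each give two-sided power for 25% against 32% of 0.98 at ICC 0.1, 0.92 at 0.3 and 0.86 at 0.5. Correct clustering would not undermine the design.

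**The case against.** The strongest reply is that the article nowhere says nets are treated as independent. It is a condensed text, a clustered variance is compatible with the words negative binomial regression, and an analysis plan that is not shown may specify one. The contrast with the hut trials is also imperfect: the sentence that lists random effects for the hut proportions names a bare negative binomial regression for mosquito entry. These points stand in part. They rule out a flat statement that the trial's standard errors will be wrong. They do not remove the mismatch: the between-arm model is fixed in print, the randomised unit is absent from it, and fitting it as named gives error bars that are too narrow.

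A reader might also infer three stronger things that the documents do not support:

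- **That the survival comparison treats nets as independent.** Only Kaplan-Meier estimation is named, with no test, standard error or interval, and within-household correlation does not by itself bias the point estimates.
- **That repeated surveys of the same net add a second layer of error.** This applies to hole area only if surveys are pooled in one model, which the article does not say. In a survival analysis each net contributes a single event or censoring time.
- **That the sample size ignores the randomised unit.** It is counted in households.

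**Conclusion.** The point holds for the hole-area comparison. As published, that model omits the unit of randomisation, and for any positive within-household correlation it rejects too often under no difference. The size is about 6% to 12% against a nominal two-sided 5%, for an assumed ICC of 0.05 to 0.3 and 3 observed nets in every household. It is modest (7.4% or less) if the ICC is at most 0.1, and smaller at late surveys as nets are lost. The ICC appears nowhere in the article, so the range illustrates the problem and does not estimate it.

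For functional survival the plan is unspecific, not wrong: the variance needs to be stated before any interval or comparison is reported. The finding concerns the validity of the analysis and not its power. If an existing analysis plan already clusters on household, citing it settles the matter.

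**What to change.** State that the negative binomial comparison of hole surface area uses household-clustered (robust) standard errors or a household random intercept. If surveys are pooled in one model, add a net-level term; if each survey is analysed separately, none is needed. For functional survival and attrition, state that any confidence interval or between-arm comparison uses household-clustered variance or a shared frailty for household. Village as a covariate is optional.

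The cost is a sentence or two of analysis wording and somewhat wider intervals: at 3 nets per household, by a factor of √1.1 = 1.05 at ICC 0.05 and √1.6 = 1.26 at ICC 0.3. No new data, visits or households are needed, because the household number is already part of each net's identifier.

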**Methods:**

The study will be conducted in parallel in selected villages in Zakpota District in Benin, Mbalmayo, District in Cameroon and Muheza District in Tanzania. In each country, ~ 1800 households will be recruited and randomised to receive DuraNet® Plus or DuraNet® (a WHO prequalified alphacypermethrin-only ITN). Follow up surveys will be performed at 1 month post distribution to investigate adverse events and subsequently every 6–12 months to assess ITN attrition and fabric integrity following standard WHO procedures. A second cohort of nets will be withdrawn every 6–12 months and assessed for alpha-cypermethrin and PBO content and for entomological activity in laboratory bioassays (cone bioassays and tunnel tests). Alpha-cypermethrin bioefficacy will be monitored using the susceptible Anopheles gambiae Kisumu strain in cone bioassays while PBO bioefficacy will be monitored using pyrethroid resistant strains with overexpressed P450 enzymes in tunnel tests to determine the proportion of efficacious nets (≥ 95% knockdown, ≥ 80% mortality or ≥ 90% blood feeding inhibition in tunnels) at each time point. Nets withdrawn at 12, 24 and 36 months from each country will also be tested in experimental hut trials against wild free-flying pyrethroid resistant Anopheles gambiae sl in Côvè Benin to investigate the superiority of DuraNet® Plus over DuraNet® at each time point under semi field conditions.

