## Background

Insecticide treated nets (ITNs) contributed > 80% to the decline in malaria burden observed in endemic countries between the years 2000 and 2015 [1]. However, progress against malaria has stalled in recent years attributable to several factors including the increasing intensity of resistance to pyrethroids; the insecticide of choice used on ITNs [2, 3].

Pyrethroid-piperonyl butoxide (pyrethroid-PBO) ITNs were developed to help maintain the effectiveness this intervention against malaria vectors that have developed resistance to pyrethroids [4]. The PBO component of the net inhibits the activity of mosquito enzymes that metabolise pyrethroids resulting in higher levels of mosquito mortality with pyrethroid-resistant mosquitoes. Community randomized-controlled trials in East Africa, have demonstrated an improved epidemiological impact against clinical malaria in communities receiving pyrethroid-PBO nets compared to standard pyrethroid-only nets [5, 6]. Based on these findings, and several experimental hut trials across Africa, the World Health Organisation (WHO) issued a conditional recommendation for their deployment in areas where vectors have developed resistance to pyrethroids [7]. This has been followed by an increased uptake of pyrethroid-PBO nets across Africa in recent years [8].

To be considered long-lasting, new ITNs are expected to demonstrate physical and insecticidal durability under operational conditions lasting at least 3 years [9–11]. Recent modelling studies have however estimated a much shorter median ITN retention time of 1.64 years across Africa [12]. ITN durability is also reported to vary from one community to another influenced by several location specific factors including, usage by householders, perceived efficacy, fabric integrity, environmental conditions etc. [11, 13]. While the WHO has recommended standardised procedures for assessing the attrition, fabric integrity, insecticidal content and bioefficacy of ITNs over 3 years of community use [9, 11], there is very limited information on the durability of pyrethroid-PBO ITNs. This is partly attributable to the fact that existing WHO ITN durability guidelines were largely tailored towards pyrethroid-only nets. Effective assessment of the durability of pyrethroid-PBO ITNs will require the development of suitable standardised methods and procedures for monitoring the bioefficacy of both active ingredients on these nets over years of field use.

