To monitor the bioefficacy of PBO in DuraNet® Plus, tunnel tests will be performed using 1 net piece from ITNs withdrawn for bioassays at 12, 24 and 36 months using the pyrethroid resistant *An. coluzzi* Akron strain (BEI resources) for Benin and Cameroon and the pyrethroid resistant *An gambiae ss* Zenet strain in Tanzania. Both strains exhibit intense resistance to pyrethroids mediated by high kdr frequencies and overexpressed P450 enzymes evidenced by increased mortality with alpha-cypermethrin following PBO pre-exposure in susceptibility bioassays. They will be fully characterised prior to each round of laboratory bioassays. The proportion of DuraNet® Plus ITNs inducing ≥ 80% mortality of the pyrethroid resistant strain in tunnel tests will also be determined for each study site. Comparison will be made with a new unused DuraNet® Plus at each timepoint. All tunnel tests will run overnight between 18:00 and 09:00 at 27 ± 2 °C and 75% ± 10% relative humidity.

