A more recent study in Uganda investigating the durability of the bioefficacy of pyrethroid-PBO nets with a pyrethroid-resistant strain with overexpressed P450 enzymes in cone bioassays and wire ball assays demonstrated a substantial decline in PBO bioefficacy over 25 months of field use [19]. However, in contrast to WHO protocols requiring that ITNs which fail to achieve efficacy criteria in cone bioassays are tested in tunnel tests [9], the study nets from the Ugandan trial were not further assessed in tunnel tests which means the durability of the PBO component may have been underestimated. Preliminary studies in Benin have also demonstrated very low ITN pass rates with pyrethroid-PBO nets against pyrethroid-resistant mosquitoes in WHO cone bioassays compared to tunnel tests (unpublished data). Tunnel tests can be more demanding, but they mimic mosquito host seeking behaviour in the presence of the net and an animal bait and thus provide more realistic bioefficacy results compared to cone bioassays. To mitigate this problem and improve the efficiency of the bioassays, in each country, we will monitor the bioefficacy of the PBO component in DuraNet® Plus directly in tunnel tests with a pyrethroid-resistant strain.

ITN physical durability studies and laboratory bioassays may not be sufficiently informative about the levels of personal and community protection against malaria that pyrethroid-PBO nets can provide to users as they age. Experimental hut trials are a suitable and reliable method for investigating the performance of indoor vector control interventions in human occupied household settings against wild free-flying mosquitoes. Recent modelling studies have demonstrated that the performance of ITNs against clinical malaria can be inferred from experimental hut trials [20]. Hence the experimental hut trials with field collected nets against wild free-flying pyrethroid-resistant malaria vectors in Benin in this protocol, will provide more insights into the potential performance of DuraNet® Plus against clinical malaria under operational use in each country. The design will also allow for a direct comparison of the potential impact of these nets at different time points post distribution from the study countries.

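### The only stated laboratory test of PBO bioefficacy is a pass/fail chi-squared test, which leaves per-net tunnel mortality unused and has little power to compare two groups of aged nets once both lie well below the 80% cut

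*Protocol article*

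**What the plan says.** In the protocol article, the section on WHO cone bioassays and tunnel tests puts one piece from each withdrawn net through a tunnel test with a pyrethroid-resistant strain at 12, 24 and 36 months. It reduces the result to a threshold: "The proportion of DuraNet® Plus ITNs inducing ≥ 80% mortality of the pyrethroid resistant strain in tunnel tests will also be determined". The comparator named there is new, unused DuraNet Plus.

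Data management and analysis then names the test for laboratory results: "A chi-squared test will be used to assess the proportion of nets of each ITN type passing the WHO criteria for alphacypermethrin and PBO bioefficacy". On numbers it says: "Data on WHO bioassays and tunnel tests will be obtained from 30 nets of each product type sampled at each time point". Table 2 agrees at 12 and 24 months but lists 50 nets per type at 36 months, at each site.

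The same paragraph treats hut-trial mortality on its full scale; those proportions "will be compared at each time point using mixed effects logistic regression". No such model is named for the laboratory tunnels.

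The abstract words the pass rule more widely, as the "proportion of efficacious nets (≥ 95% knockdown, ≥ 80% mortality or ≥ 90% blood feeding inhibition in tunnels) at each time point". The methods section gives mortality alone for PBO.

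**The concern.** A tunnel test yields a count of dead mosquitoes out of those exposed. The stated test keeps only which side of 80% each net fell on. For the susceptible-strain test of alphacypermethrin that cut is the established WHO criterion. For PBO it is carried over to an intensely resistant strain, and the Background itself says that "existing WHO ITN durability guidelines were largely tailored towards pyrethroid-only nets".

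The study aims to describe durability over three years in three countries. If aged nets at two time points, or from two sites, both mostly fail, a further real fall in activity leaves the two pass rates almost equal. A non-significant result would then reflect the threshold and could be misread as stable PBO activity.

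**Working it through.** **Plan's own figure.** The article states no power, effect size or between-net variation for the bioassays. Its only sample-size calculation concerns functional survival and does not bear on this point. Table 2's laboratory total is consistent: 6 × 30 + 50 = 230 nets per type per site. The PBO tunnel rounds at 12, 24 and 36 months thus use 30, 30 and 50 nets.

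**Inputs.**
- Pass rule: at least 80% mortality (methods section).
- Nets: 30 per group; 50 at 36 months as a variant.
- Mosquitoes per net: 100. This is stated for the susceptible strain only and is assumed here for the resistant strain.
- Mean mortality and intra-net correlation ρ (0.05, 0.10, 0.20): assumed.

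**Why the test stalls.** If group B has 0 passes of 30 and group A has x of 30, the Pearson statistic is 60x/(60 − x). For x = 3 it is 180/57 = 3.16; for x = 4 it is 240/56 = 4.29. The 5% critical value is 3.84, so at least 4 passes against 0 are needed. At ρ = 0.10, mean mortality of 50% gives a pass rate of about 3%, or 30 × 0.03 = 0.9 nets; 35% gives about none. Four against zero is then rare, although the true means differ by 15 points.

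**Simulation.** Each net's true mortality is drawn from a beta distribution with the given mean and ρ, and deaths are binomial out of 100. Two-sided 5% tests: Pearson chi-squared on pass/fail, and a Welch t-test on each net's empirical logit, standing in for a regression on counts. Power for ρ = 0.05/0.10/0.20, 30 v 30 nets:

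| Mean mortality | Chi-squared, % | Full scale, % | Loss, points |
|---|---|---|---|
| 85 v 75% | 89/67/43 | 98/87/66 | 9/20/23 |
| 70 v 60% | 52/41/29 | 90/67/44 | 38/26/15 |
| 50 v 35% | 0/2/22 | 100/94/73 | 100/92/51 |

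Repeat runs agree within about 2 points. With equal means of 80% both tests reject about 5% of the time.

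**More nets.** With 30 v 50 nets, 70 v 60% gives 61/53/37 v 96/78/52, and 50 v 35% gives 0/8/33 v >99/98/82. Pooling three sites (90 v 90), 50 v 35% gives 0/30/60 v about 100.

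**Other parameterisation.** With a between-net SD of 0.15 and a 15-point difference (30 v 30), chi-squared v full-scale power is 91 v 95% at 80 v 65%, 60 v 95% at 65 v 50%, and 1 v 95% at 50 v 35%. With SD 0.20 it is 54 v 79% at 65 v 50% and 13 v 79% at 50 v 35%. With 50 mosquitoes per net and SD 0.15, 50 v 35% gives 2 v 93%.

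**The comparison the article names.** Take 30 new DuraNet Plus nets, assumed at 90% mortality, against 30 aged nets. Chi-squared power is 100/95/79% with aged nets at 75%, and about 100% with aged nets at 60%. Here falling below the cut helps the test, because the pass rates move apart.

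**The case against.** Five objections deserve an answer.

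- **Named comparator.** A reader might infer that the chi-squared test loses most of its power whenever aged nets drop below 80%. That does not hold for aged against new DuraNet Plus, the only comparator named for the PBO tunnels. The article also does not say that the chi-squared test is meant to compare time points or sites. This stands, and confines the point to two aged groups.
- **Expected mortality.** A reader might infer from the cited Ugandan study, which "demonstrated a substantial decline in PBO bioefficacy over 25 months of field use", that tunnel mortality of 35 to 60% is to be expected. That study used cone and wire ball assays. The Discussion says its lack of tunnel tests may have led to PBO durability being underestimated, and that cone pass rates were very low compared with tunnels. It supports a decline, not a level of tunnel mortality. This stands.
- **Other outcomes.** Hut mortality is already modelled over time and between countries, and PBO content is measured at 12, 24 and 36 months. The hut model does not make the laboratory plan contradictory, since these are different assays. But the huts use one wild population in Benin, whereas the tunnels run in each country, so they do not replace the tunnel result.
- **Wider pass rule.** If the abstract's feeding-inhibition route counts for PBO, pass rates could be higher than simulated. The outcome would still be one yes/no result per net.
- **Unseen analysis plan.** A supplementary model may be specified there. That limits how firmly one can say pass/fail is the sole analysis; it remains the only one the article states.

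**Conclusion.** The point holds in a conditional form. The only stated laboratory inference for PBO discards recorded per-net mortality. The cost depends on the comparison:

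- Aged against new DuraNet Plus, with new nets above the cut: the test is adequate.
- Two aged groups near the cut: a moderate loss, 9 to 23 points at 85 v 75%.
- Two aged groups well below it: most or nearly all of the power, 51 to 100 points at 50 v 35%.

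The same applies to a comparison of the two net types if aged DuraNet is also tested against the resistant strain, which the article leaves unclear. All sizes rest on assumed means, correlations and mosquito numbers. Nor is a full-scale analysis a complete remedy: at 70 v 60% with ρ = 0.20 its own power is only 44%. A reader might conclude that the pass/fail test should be removed. The documents do not support that, because the pass proportion is the declared efficacy measure.

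**What to change.** In Data management and analysis, keep the pass proportion and its chi-squared test as the WHO-style summary. Leave the susceptible-strain criteria unchanged. Add, as the analysis of PBO decline, a mixed-effects logistic (or beta-binomial) regression of number dead out of number exposed in the resistant-strain tunnels, with:

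- a net-level random effect, or an overdispersion term;
- months since distribution, site and their interaction;
- the concurrently tested new DuraNet Plus as the reference at each round and site.

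The last term is essential. The strain in Tanzania differs from that in Benin and Cameroon, and the Discussion accepts that laboratory strains can change over time. Without a concurrent reference, such differences would be read as PBO decline. State how many new nets are tested per round, since the comparison above assumed 30. Also reconcile the 30 nets in the text with the 50 in Table 2, and the abstract's pass rule with that in the methods section.

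The counts are needed anyway to decide a pass, and the model type is already planned for the huts, so the cost is mainly analysis wording. The small downside is that the result is an odds ratio, so pass rates must be shown alongside it.
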